### Intervention

#### Control group

Participants allocated to the control group will continue to receive standard/usual care as determined by their treating healthcare professionals. That is participation in the study will not preclude them from their usual care. They will not have access to the digital peer support app because it is not publicly available.

#### Peer support intervention

Participants will have access to a 6 months mobile application (digital) peer support programme. The intervention aims to enable peer support among people with lived experience of heart disease via an online community forum. Details of the intervention are provided in table 1 based on the TIDieR checklist.^31^ On commencing the intervention period, participants will download the free application and register their details. Participants will then be able to access information and resources, select different discussion groups (general, diet and exercise, thinking and memory) based on topics of interest and interact with each other (table 1). All participants will have access to all Discussion Groups and will not be matched into pairs but form a large group. Registered health providers will be available to moderate the community topic discussions. Participants will also be provided with the Heart2Heart Peer Support Guide (Portable Document Format, PDF) via the mobile application in the resources tab. The Guide outlines the ground rules for participating in peer support sessions. Participants will also be asked to review the University of Sydney Privacy Policy, which outlines how their personal information will be used and protected.

**Table 1 T1:** Overview of Heart2Heart intervention*

What	Access to a digital peer support app with four components; Discussion Groups with other people with lived experience of heart disease. The app has three primary discussion groups where participants can go online and introduce themselves and share their (1) general experiences relating to their heart disease journey and care, (2) exercise and diet and (3) memory and thinking. Participants will be able to freely move in and out of these discussion groups depending on their own preference. Ask an expert’ sessions that mimic those commonly available at the in-person peer support group. These sessions will be scheduled monthly for 30 min and include sharing of advice by multidisciplinary clinicians (registered with national relevant national authorities) such as nurses, allied health providers, dietitians and pharmacists. Participants will also be able to ask questions about topics such as exercise and diet, medicine and cognition. Resources are available via virtual folders in the app. Resources include videos and ‘fact sheets’ developed by the National Heart Foundation of Australia, peer support guidelines, the privacy policy and study documents. Fact sheets include resources relating to heart disease risk factors, medications and cardiac rehabilitation. The peer support guidelines cover aspects related to being respectful, inclusive and using appropriate language, promoting a supportive and welcoming community, encouraging a safe space, showing respect and empathy, using language carefully, listening to others a safe space where individuals feel comfortable sharing their stories and challenges.
Who	As a peer support intervention, the intervention is largely driven by conversations and input of other participants who also have lived experience of heart disease. However, the research team will monitor daily for inappropriate content (such as aggressive or inappropriate language or behaviour) and to help facilitate positive and supportive online conversation although content will be driven by the participants themselves.
How	The intervention is delivered online via a stand-along app that is only available to people allocated to the intervention group of this study. It is freely available and has a password-protected login. There is no face-to-face component.
When	Once signed into the app, participants can login and use it as much or as little as they choose for 12 months. There are no limits to time spent using the app although the study will track usage frequency and time spent in the app.
Tailoring	There is no personalised tailoring within the intervention

* Based on the Template for Intervention, dDescriptor and rReplication (TIDieR).^31^

### Data collection and study outcomes

The data collection schedule and time points for each outcome are summarised in table 2. Data will be collected remotely and entered into a purpose-built online questionnaire using the REDCap software.

**Table 2 T2:** Schedule of Heart2Heart study procedures

	Time point (months)		
Schedule of assessments	0	6	12
Eligibility screen	✓		
Informed consent	✓		
Randomisation/allocation	✓		
Primary outcome			
Social connection in the context of cardiovascular health	✓	✓	✓
Secondary outcomes			
Social connectedness—8-item Social Connectedness Scale^33^	✓	✓	✓
Proportion physically inactive—GPAQ score^34^	✓	✓	✓
Proportion physically inactive—METs accelerometer (10% of participants)	✓	✓	
Point abstinence from smoking—self-report	✓	✓	✓
Proportion of participants consuming alcohol one or more standard drinks per week—self report	✓	✓	✓
Proportion of participants meeting fruits and vegetable guidelines—self-report	✓	✓	✓
Proportion of days covered with guideline-recommended medications—Pharmaceutical Benefits Scheme administrative data	✓	✓	✓
All-cause and CVD hospitalisations—self-report		✓	✓
All-cause and CVD mortality—National Death Index		✓	✓
Health Service Utilisation (medical appointments, cardiac rehabilitation, peer support programmes)—Medicare Benefits Scheme administrative data and self-report	✓	✓	✓
PROMs and PREMs			
Self-efficacy—Self-Efficacy to Manage Chronic Disease Scale—six item^35^	✓	✓	✓
Quality of life—EQ5D-5L^36^	✓	✓	✓
Participant satisfaction/acceptability with peer support programme—purpose built survey	✓	✓	
Digital peer support usage and engagement—analytical app data (page visit, frequency of login, participation in discussion groups, etc) for intervention participants only		✓	

CVDcardiovascular diseaseEQ5D-5LEuroQol 5 dimensionGPAQ, Global Physical Activity QuestionnaireMETsmetabolic equivalentsPREMspatient-reported experience measuresPROMspatient-reported outcome measures

The primary outcome is the proportion of participants who feel socially connected at 6 months follow-up. The primary outcome was selected to reflect the primary intent of the intervention and as a measure of the functional aspects (accessibility and utilisation of support) of social connection are the focus rather than structural aspects (eg, household numbers).^32^ The primary outcome is a composite of self-reported affirmative responses to two items related to functional social connection in the context of a person’s heart health and have been adapted from a validated survey.^33^ The two items are (1) ‘When it comes to my heart health, I am able to connect with other people’ and (2) ‘When it comes to my heart health, I have a sense of togetherness with my peers’. Response options for each item are ‘definitely not’, ‘probably not’, ‘maybe’, ‘yes, probably’ and ‘yes definitely’. Participants who report ‘yes probably’ and ‘yes definitely’ will be counted to the primary outcome.

Secondary outcomes (table 2) are differences in; mean aggregate social connectedness scale^33^ score, hospital admissions (all-cause and CVD), mortality, lifestyle (physical inactivity based on Global Physical Activity Questionnaire,^34^ not smoking, sufficient fruit and vegetable consumption), proportion taking guideline-indicated medications and health service utilisation (medical appointments, cardiac rehabilitation, community-based peer support programmes) between the control and intervention groups at 6 and 12 months. Patient-reported outcome and experience measures (table 2) are self-efficacy (Self-Efficacy to Manage Chronic Disease Scale,^35^ quality of life EQ5D-5L,^36^ satisfaction and programme (peer support engagement at 6 months)). Process measures will include application analytics, fidelity of the intervention and barriers and enablers to engagement from the perspective of participants allocated to the intervention group.

To verify self-reported physical activity data, a random subset (minimum 10%) of participants (control and intervention), physical activity will be assessed over 24 hours per day for 7 days (prior to baseline randomisation for baseline data), using a GENEActiv V.1.2 wrist-worn sensor which collects continuous accelerometry data via bluetooth. The sensor does not provide feedback to the wearer (no screen), minimising the likelihood of participants’ physical activity being influenced by sensor information. Sensors will be sent to and from participants via mail in a reply-paid envelope, along with instructions on how and when to wear the activity sensor and a logbook to record date and times worn or removed. Once the sensor and logbook are returned, the research team will download data from the tracker in real-time for storage in the study database. These data will be analysed by comparing average minutes per day participant were at least moderately physically active and be the subject of a sensitivity analysis to provide verification of the self-reported physical activity data.

An evaluation of the fidelity and barriers and enablers to delivery of and engagement with the digital peer support programme; a series of process measures will also be collected. A mixed-method approach will be used with four sources: (1) quantitative data from the app analytical data logs related to consumer engagement, participation in virtual communities, frequencies of logins, time spent on the app, rate of opening of resources within the peer support app and content of posts and responses; (2) focus groups with a subset of participants (all in intervention invited then from those who agree we will recruit consecutively until thematic saturation is achieved) in the intervention group to understand satisfaction with digital peer support, potential utility and suggestions for improvement and (3) semistructured interviews with a proportion of cardiac rehabilitation coordinators (all those from cardiac rehabilitation programmes who recruited participants will be invited) and stakeholders from not-for-profit peer support organisations (online search of Australian peer support associations for heart disease) to explore, from a clinician perspective, the usefulness of peer support, challenges to delivery, resources needed and requirements for implementation if such a programme was to be made routinely available. Sample sizes for the focus groups and semistructured interviews will be based on thematic saturation; however, based on prior experience,^37^ we anticipate that we will require at least four focus groups (6–8 participants per group) and 10 interviews.

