### Participants and recruitment

Inclusion criteria are people (1) aged at least 18 years; (2) with a confirmed diagnosis of heart disease, coronary revascularisation procedure or greater than 50% stenosis on coronary angiogram within the prior 12 months and (3) own a mobile device. Exclusion criteria are people (1) with major neurocognitive diagnoses; (2) who are not willing/able to give informed consent and (3) are unable to read or speak English.

Three recruitment strategies will be used to allow varied identification of potential participants via peer support associations, cardiac rehabilitation programmes and direct to consumers. The strategies are as follows: (1) consumer-focussed stakeholder organisations will email members with information about the study and if interested, potential participants can contact the research team for screening and to explore interest in participation; (2) the research team will contact community peer support programmes and promote the study via social media to introduce the trial to explore potential eligibility and interest of eligible people in participating and (3) cardiac rehabilitation coordinators in participating states will identify potential participants from their programmes over the previous 6 months. Research staff will then contact them in-person, via telephone or email to screen for eligibility and explore potential willingness to participate in the study. For all prospective participants, a research staff member will seek consent (online supplemental file 2) (either on paper or e-consent or directly via the mobile application) prior to baseline data collection and randomisation. Taken together, the collective cardiac rehabilitation programmes have approximately 1000 eligible people, the Australian stakeholder organisations have a membership base of over 1000 and the community peer support programmes include an online group (MyHeartMyLife) with approximately 3800 members.

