### Sample size and statistical analyses

A sample size of 752 (376 per group) will achieve over 80% power, allowing for 10% drop-out, to detect a difference in the proportion of participants that feel socially connected between control and intervention groups by 10% at 6 months follow-up where the baseline estimate is based on the British Regional Heart Study, where 27% of participants with pre-existing CVD were classified as having low social engagement.^38^ As reported in a recent scientific state from the American Heart Association, there is consistent evidence for a direct association between social isolation, loneliness and CHD and stroke mortality, but the relationship is complex with unmeasured confounders.^39^ Based on advice from expert clinicians in the area, it was determined that an effect of reduced social isolation for one in 10 people would be clinically meaningful and hence an effect size of 10%.

Analyses will be performed according to the intention-to-treat principle by a statistician blinded to group allocation. Baseline and outcome data will be presented as frequencies and proportions for categorical data and means and SD for normally distributed continuous outcomes or median and IQR intervals for skewed continuous outcomes. Outcomes will be compared between control and intervention groups using all available data with intervention and control groups compared at 6 and 12 months. Normally distributed continuous outcomes will be analysed using the analysis of covariance and categorical outcomes will be compared using a log-binomial regression model, adjusting for baseline value of the outcome variable. Prespecified subgroup analyses will be performed for (1) self-reported gender, (2) regional areas, (3) cardiac rehabilitation completion (at least 50% of sessions offered) versus not and (4) previous or current peer support attendance (has participated in an in-person or other digital peer support programme since January 2024) versus not. The subgroups will be compared by including an interaction term between the subgroups and the randomisation status to the main models as described above.

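### The implied smoking analysis fits one risk ratio for abstinence across baseline smokers and non-smokers; non-smokers near 100% hold it close to 1, so a real effect on quitting would read as a precise null.

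*Protocol article*

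**What the plan says.** In the protocol article, Table 2 (under Data collection and study outcomes) schedules "Point abstinence from smoking—self-report" at 0, 6 and 12 months. The text of that section lists the lifestyle outcomes as physical inactivity, "not smoking, sufficient fruit and vegetable consumption", compared between the arms at 6 and 12 months. Neither place limits the outcome to people who smoke at entry.

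Under Participants and recruitment, entry is for adults "with a confirmed diagnosis of heart disease, coronary revascularisation procedure or greater than 50% stenosis on coronary angiogram within the prior 12 months" who own a mobile device. Smoking status is neither an inclusion nor an exclusion criterion.

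Under Sample size and statistical analyses, "Outcomes will be compared between control and intervention groups using all available data", and "categorical outcomes will be compared using a log-binomial regression model, adjusting for baseline value of the outcome variable". Baseline smoking is not among the four prespecified subgroups. The sample size covers the primary outcome only, and no power is stated for smoking.

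**The concern.** A log-binomial model with terms for arm and month-0 smoking, and no interaction, estimates one risk ratio that must serve both strata. Month-0 non-smokers are nearly all abstinent at follow-up, so their proportion has almost no room to rise. On the log-risk scale they also carry nearly all the information. A treatment effect confined to smokers therefore hardly moves the estimate.

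This goes beyond low power. The reported ratio would be about 1.00 with a tight interval, and a reader would take that as good evidence that the app does not affect smoking. The interval would mainly reflect non-smokers staying non-smokers. Behavioural risk is part of the trial's stated aim, so this null would be read and cited.

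**Working it through.** **Inputs from the article.** "A sample size of 752 (376 per group) will achieve over 80% power, allowing for 10% drop-out"; difference "between control and intervention groups by 10% at 6 months follow-up"; reference figure "27% of participants with pre-existing CVD were classified as having low social engagement". Alpha is not stated; two-sided 0.05 is assumed.

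**The plan's own figure.** The pooled-variance formula for 27% v 37% at 80% power gives (1.960 × √(2 × 0.32 × 0.68) + 0.842 × √(0.27 × 0.73 + 0.37 × 0.63))² / 0.10² = 340.4, so 341 per arm. 341 × 1.1 = 375.1, rounded up to 376 per arm, or 752 in total. The stated size is reproduced. The number analysed is 376 × 0.9 ≈ 338 per arm.

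**Inputs the documents do not give (assumed).** 8–20% smoke at month 0; 1–3% of month-0 non-smokers smoke at follow-up, equally in both arms; among month-0 smokers, quitting is 20% in control and 40% with the app.

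**Step 1: the cap.** No fitted probability may exceed 1, so (control abstinence in non-smokers) × RR ≤ 1. At 99% abstinence RR ≤ 1/0.99 = 1.01; at 97% RR ≤ 1/0.97 = 1.03. The true ratio among smokers is 0.40/0.20 = 2, which this model cannot express.

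**Step 2: where the information sits.** Take 10% smokers (34 per arm, leaving 304 non-smokers) and 2% relapse. The variance of a log risk is (1 − p)/(np), and a common ratio is close to the inverse-variance average of the two strata.

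| Event | Stratum | Variance of log RR | Weight | Stratum RR |
|---|---|---|---|---|
| Abstinent | Non-smokers | 2 × 0.02/(304 × 0.98) = 0.000134 | 7,448 | 1.00 |
| Abstinent | Smokers | 0.8/(34 × 0.2) + 0.6/(34 × 0.4) = 0.162 | 6.2 | 2.00 |
| Smoking | Non-smokers | 2 × 0.98/(304 × 0.02) = 0.322 | 3.1 | 1.00 |
| Smoking | Smokers | 0.2/(34 × 0.8) + 0.4/(34 × 0.6) = 0.0270 | 37.1 | 0.75 |

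- Abstinence as event: smokers carry 6.2/7,454 = 0.08% of the weight. RR = exp(0.0008 × ln 2) = 1.001; SE = 1/√7,454 = 0.0116; 95% interval about 0.98 to 1.02.
- Smoking as event: smokers carry 37.1/40.2 = 92%. RR = exp(0.923 × ln 0.75) = 0.77; SE = 1/√40.2 = 0.158; 95% interval about 0.56 to 1.04.

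The participants, data and covariate are the same in both rows. Only the event differs.

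**Step 3: simulation over the assumed ranges** (338 per arm, quitting 20% v 40%).

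| Analysis | Significant | RR |
|---|---|---|
| Implied model: everyone, abstinence, adjusted | 3–9% | median 1.00 |
| Everyone, current smoking as event, adjusted | 33–69% | about 0.77 |
| Month-0 smokers only | 32–71% | – |

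Over a wider grid (5–30% smokers, 1–5% relapse, quitting doubled from 10%, 20% or 30%) the implied model stays at about 3–11%, with a mean ratio of 1.00 to 1.01.

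**Step 4: what 80% power would take.** Smokers only, 20% v 40%, needs 82 smokers per arm. 82/338 = 24% of those analysed.

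**The case against.** **The denominator is inferred.** No sentence says that everyone is scored. The neighbouring alcohol and diet rows of Table 2 refer to a proportion of participants, while the smoking row does not. The baseline-adjustment sentence is generic and cannot apply literally to every outcome, since mortality has no month-0 value. An analysis plan not shown may be more specific. This stands as a caution. Even so, the all-participant reading is strongly implied: among month-0 smokers the baseline value is constant, and adjusting for it would mean nothing.

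**A reader might infer that including people who do not smoke is itself the error.** The documents do not support that. Non-smoking among everyone randomised is a legitimate intention-to-treat outcome. With diagnosis or a procedure within the prior 12 months, month-0 non-smokers may include recent quitters, for whom staying abstinent is a fair aim of peer support. Table 2 of the working above also shows that keeping everyone costs little once smoking is the event: 33–69% against 32–71% for smokers only. The fault is a common ratio on a near-ceiling event.

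**A reader might also infer that no whole-sample comparison could show a doubling of quitting.** That is too strong. An unadjusted comparison reaches 70% power with 20% smokers and quitting of 30% v 60% (no relapse). A robust-variance Poisson model with the same adjustment gives 8–45% at 10% smokers and 26–97% at 30%. The near-invisibility belongs to the log-binomial model for abstinence that the text implies.

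**This is one secondary outcome with no power claimed, and a doubling is generous for an untailored app.** Both points are fair and limit the weight of the finding. Low power alone would be no complaint. The problem is a falsely narrow interval around 1.

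**Conclusion.** The point holds in a limited form. As the article reads, the smoking outcome would be analysed with a model whose treatment ratio is held near 1 by month-0 non-smokers, largely regardless of what happens to smokers. Under the assumed inputs it is significant in about 3–9% of trials, close to the false-positive rate, although quitting has doubled.

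The cap needs only one assumption, that nearly all month-0 non-smokers stay abstinent. The percentages rest on smoking prevalence, relapse and quit rates that the documents do not give, and on equal relapse in both arms. The primary outcome and the sample size are unaffected.

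**What to change.** State in the protocol or analysis plan that:

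1. the main smoking comparison keeps all randomised participants with data and models current smoking at 6 and 12 months as the event, adjusted for month-0 smoking;
2. abstinence at 6 and 12 months among month-0 smokers, by randomised arm, is a prespecified supporting analysis (month-0 status precedes randomised treatment, so the comparison stays randomised);
3. smoking at follow-up among month-0 non-smokers is reported separately by arm.

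This costs a few sentences and no new data, since smoking is already scheduled at month 0. The smokers-only comparison would rest on about 27–68 people per arm (8–20% of 338), so its interval will be wide. Neither analysis is assured 80% power, and the text should not suggest otherwise.

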### Data storage and management

De-identified data will be stored in the University of Sydney’s Research Data Store which is password protected. Identifiable information such as names, contact details, date of birth and post code will be removed from the data and be replaced with a participant ID number. Identifiable information will be stored separately from the clinical data on a locked electronic file location, which is only accessible by the research team.

### Sample size and statistical analyses

A sample size of 752 (376 per group) will achieve over 80% power, allowing for 10% drop-out, to detect a difference in the proportion of participants that feel socially connected between control and intervention groups by 10% at 6 months follow-up where the baseline estimate is based on the British Regional Heart Study, where 27% of participants with pre-existing CVD were classified as having low social engagement.^38^ As reported in a recent scientific state from the American Heart Association, there is consistent evidence for a direct association between social isolation, loneliness and CHD and stroke mortality, but the relationship is complex with unmeasured confounders.^39^ Based on advice from expert clinicians in the area, it was determined that an effect of reduced social isolation for one in 10 people would be clinically meaningful and hence an effect size of 10%.

Analyses will be performed according to the intention-to-treat principle by a statistician blinded to group allocation. Baseline and outcome data will be presented as frequencies and proportions for categorical data and means and SD for normally distributed continuous outcomes or median and IQR intervals for skewed continuous outcomes. Outcomes will be compared between control and intervention groups using all available data with intervention and control groups compared at 6 and 12 months. Normally distributed continuous outcomes will be analysed using the analysis of covariance and categorical outcomes will be compared using a log-binomial regression model, adjusting for baseline value of the outcome variable. Prespecified subgroup analyses will be performed for (1) self-reported gender, (2) regional areas, (3) cardiac rehabilitation completion (at least 50% of sessions offered) versus not and (4) previous or current peer support attendance (has participated in an in-person or other digital peer support programme since January 2024) versus not. The subgroups will be compared by including an interaction term between the subgroups and the randomisation status to the main models as described above.

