### Randomisation and blinding

After informed consent, participants will be randomised and directed electronically to the online data collection survey. Randomisation will be stratified by regional/rural and urban areas and by those recruited from in-person peer support networks versus not (50:50). An independent statistician will generate the randomisation schedule (then upload into the study Research Electronic Data Capture, REDCap) with allocation sequence concealment strategies implemented. This is single-blind study where investigators, statisticians and research assistants collecting data will be blinded to group allocation; however, participants will know if they are allocated to the digital peer support intervention.

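### The stated analysis models adjust only for the baseline value and leave out both randomisation stratification factors: no bias, a small loss of precision, and a free improvement

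*Protocol article*

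**What the plan says.** Protocol article, Randomisation and blinding: "Randomisation will be stratified by regional/rural and urban areas and by those recruited from in-person peer support networks versus not (50:50"). Two factors therefore constrain the allocation.

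Protocol article, Sample size and statistical analyses: continuous outcomes go to analysis of covariance, and "categorical outcomes will be compared using a log-binomial regression model, adjusting for baseline value of the outcome variable". No other covariate is listed for the main models.

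The same section prespecifies four subgroup analyses by interaction with randomised group. One is regional area. Another is previous or current peer support attendance, in person or through another digital programme, since January 2024. That is not the same variable as having been recruited from an in-person network.

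On size and scale, the section plans the trial "to detect a difference in the proportion of participants that feel socially connected between control and intervention groups by 10% at 6 months follow-up". It justifies this by a benefit to one person in ten, which "would be clinically meaningful and hence an effect size of 10" per cent. It states that "A sample size of 752 (376 per group) will achieve over 80% power, allowing for 10% drop-out". It names no effect measure for reporting, and says that outcome data will be shown as frequencies and proportions.

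**The concern.** Stratified randomisation forces the arms to be balanced on the stratification factors. If those factors predict the outcome, the treatment estimate varies less between hypothetical repetitions of the trial than a model without them assumes. The reported standard error is then too large, the test rejects less often than its nominal level, and power is given away.

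The recruitment factor is plausibly prognostic here. One of the two primary outcome items asks about a sense of togetherness with peers, and people recruited from in-person peer groups may answer it differently from others. That is an inference: the article gives no figure for it.

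The article states its covariate set, so this is a choice that does not match the design and not merely a detail left for later. At stake is a little precision on the primary outcome in a trial planned close to 80% power. The validity of the comparison is not in question.

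**Working it through.** **1. The plan's own figure.** Inputs from Sample size and statistical analyses: 376 per group, 80% power, 10% drop-out, a 10-point difference, and the 27% figure. Alpha is not stated; 0.05 two-sided is assumed. With unpooled variance and 27% versus 37%:

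n = (1.960 + 0.842)² × (0.27×0.73 + 0.37×0.63) / 0.10² = 7.849 × 0.4302 / 0.01 = 337.7, so 338 per group.

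338 / 0.9 = 375.6, so 376 per group and 752 in total. This matches. 63% versus 73% gives the same number. 73% versus 83% would need about 598 in total (269 per group with pooled variance, 299 after drop-out). The check below therefore uses control rates of 27%, 63% and 73%. About 676 participants (2 × 338) are analysed.

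**2. Where each stratification factor appears.**

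| Factor | Main models | Subgroup models |
|---|---|---|
| Regional/rural vs urban | no | yes, as an interaction |
| Recruited from in-person peer network vs not | no | no (the peer attendance subgroup is defined differently) |

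**3. Size of the loss, by simulation.** Assumed, because the documents give no values: the strength of the stratum effects, and a latent correlation of 0.5 between baseline and 6-month answers. Set-up: 676 analysed, blocked stratified allocation, baseline value in the model, robust-variance Poisson in place of log-binomial, 800 trials per setting, rates 27→37, 63→73 and 73→83.

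| Assumed stratum effects (latent SD) | Excess SE, baseline-only model | Power gained by adding strata |
|---|---|---|
| one weak factor (0.3) | 0.3–1.0% (both of the first two rows) | −0.1 to +0.2 points |
| moderate (0.2 and 0.5) | 0.3–1.0% | +0.2 to +0.9 points |
| very strong (0.5 and 0.8) | 2–3% | +0.7 to +1.7 points |

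A second simulation, also with the baseline value included, gave a standard error about 1–3% larger and a power gain of about 0–1 point. One power estimate from 800 trials has a Monte Carlo standard error of √(0.8×0.2/800) = 1.4 points, so these gains are orders of magnitude.

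**4. Cross-check by formula.** Suppose the reported standard error is k times the true one and the trial has 80% power when k = 1. Then power = Φ(2.802 − 1.960k) and two-sided type I error = 2[1 − Φ(1.960k)].

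- k = 1.01: Φ(0.822) = 79.4%, a loss of about 0.6 points; type I error 4.8%.
- k = 1.03: Φ(0.783) = 78.3%, a loss of about 1.7 points; type I error 4.4%.

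This agrees with the simulated 0–2 points and shows the direction: conservative.

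**5. Without the baseline covariate (not the stated model).** With 1,500 runs per setting and each factor shifting the outcome by 20 points, type I error was 4.1–4.3% without strata and 5.2–5.3% with them. Power was 78.5–79.9% and 82.3–82.6%. With 10-point shifts the gain was about 1 point, and with no shift it was nil. The 20-point gain of roughly 3–4 points overstates the loss for this plan, because the baseline value already carries part of what the strata predict.

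**6. Scale.** A 10-point gain is a risk ratio of 0.37/0.27 = 1.37, 0.73/0.63 = 1.16 or 0.83/0.73 = 1.14. The same absolute target maps to quite different ratios. For power the scale hardly matters: with 338 per group at 27% versus 37%, it is 79.7% for the difference (pooled test) and 78.8% for the log risk ratio. Both test equality of proportions.

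**The case against.** The strongest reply is that the effect is small and rests on invented stratum effects, that the error is in the safe direction, and that a full analysis plan may already list the factors. The first two parts stand, and they are why this is an improvement and not a flaw. The third is possible, but the article does state its covariate set, and that set omits both factors. If the analysis plan includes them, only the published description needs to agree.

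A reader might also infer more than the document supports:

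- **That the plan yields only a risk ratio, which cannot be read against the 10% target.** The article names a model and no effect measure. It will present outcome proportions, from which the crude difference follows, and an adjusted difference can be standardised from the same fit.
- **That the log-binomial model as specified is unstable.** The failures seen (2–6% of runs at 73/83, 20% at 90/93) arose in a log-binomial model with the strata added, which the article does not specify. They bear only on how to carry out the fix, and 90/93 is not a scenario in the document.
- **That the standard error is 5% too large and over 3 points of power are lost.** This comes from 50→60 with strongly prognostic strata (0.0667/0.0635 = 1.05; 76.6% versus 80.1%). Those rates are not design figures of this trial.
- **That the test is biased or the sample size invalid.** Neither follows. Omitting the strata makes the test conservative, and the change of scale costs at most about 1 point of power.

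**Conclusion.** The point holds as a modest one. The stated main models omit both factors used to stratify randomisation, and the subgroup interactions do not supply them. The treatment comparison remains unbiased. With the baseline value in the model, the expected cost is a standard error about 1–3% too large and roughly 0–2 points of power, or nothing if the strata are not prognostic.

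These figures assume two-sided 5% testing, 676 analysed, and stratum effects and a baseline correlation that the documents do not give. The loss is of some interest because 752 reproduces at almost exactly 80% power from 27% versus 37%, which leaves little slack. If the true rates are nearer 73% versus 83%, power is about 88% and the loss matters less.

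The mismatch between an absolute target and the model's native risk ratio is a secondary reporting point. It is a free improvement and not an error.

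**What to change.** In the statistical analysis plan, before unblinding:

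1. Add region (regional/rural versus urban) and recruitment source (in-person peer support network versus not), as used in the randomisation, to the primary and secondary models beside the baseline value. This applies to both the analysis of covariance and the log-binomial model.
2. Name a fallback for when the log-binomial model does not converge, such as Poisson regression with robust variance. It is needed because adding covariates makes convergence harder at high prevalence.
3. For the primary outcome, report an adjusted risk difference with 95% CI, obtained by standardisation, beside the risk ratio, so that the result can be set directly against the 10-point target.

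The cost is a few sentences. Both factors are known at randomisation, so no new data and no change to the sample size are needed.
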